#### Statistical analysis plan

All statistical analysis plans (SAPs) will be drafted early in the study and finalized before the analysis of unblinded data.

The primary clinical efficacy analysis will use a linear mixed effects model with the dependent variable being the change in RVSV (flow) from baseline to 12 weeks. “Baseline” and “12 weeks” refer to the time points within each treatment period. Each participant will contribute up to two observations if they complete both treatment periods. A random effect for each participant will be included together with the within‐treatment period baseline RVSV (flow) measurement, a fixed period effect, and treatment (selexipag or riociguat) allocated during the treatment period. This model will be used to estimate the mean difference between the two treatment approaches (ERA + sGCS and PDEi + ERA + IP receptor agonist), together with a 95% confidence interval and a *p* value using a Wald test.

Similar methods will be applied to the analysis of secondary efficacy outcomes. Treatment effect heterogeneity between subgroups will be assessed by including treatment‐by‐subgroup interaction terms in regression models. Main analyses will use complete data only, but multiple imputation will be used for missing data in sensitivity analyses. No adjustments will be made for multiple statistical tests. All efficacy analyses will follow the intention to treat principle (i.e., analysis according to randomized treatment, regardless of treatment compliance). Safety data (adverse events and side effects) will be summarized in relation to treatment being received at the onset of the event, and the study period (pretreatment period 1, treatment period 1, washout period, treatment period 2, posttreatment period 2); no formal statistical comparisons will be applied.

To analyze whether changes in RVSV (flow) may be explained by remotely monitored physiological parameters, we will test whether there is a significant correlation between the change between baseline and Week 4/Week 8 physiological parameters and the change between baseline and Week 12 RVSV (flow) outcome. We will also adopt a mediation analysis approach to investigate what proportion of the change between baseline and Week 12 RVSV (flow) is explained by the change between baseline and Week 4/Week 8 physiological parameters using the mediation package in R. Secondary endpoints will be analyzed using appropriate regression models.

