### Study population

The study aims to recruit 40 patients with PAH, established on PDE5i and ERA, through the UK National Pulmonary Hypertension Clinical Studies Network (UNIPHY)—a collaboration of UK centers commissioned for the treatment of PAH, providing access to all patients within the UK currently receiving targeted therapy for PAH (>5000).^32^, ^33^ Suitable patients will be identified from existing patient lists by local teams and invited to screening via clinical and research teams.

Eligible patients meeting the inclusion and exclusion criteria (Table 2) will be established on PDE5i/ERA dual therapy and will meet NHS England's National Commissioning and ESC guideline criteria for initiation of IP receptor agonist or sGCS.^2^, ^9^, ^10^ While it is expected the majority of patients recruited will have intermediate‐low risk PAH, patients with intermediate‐high risk PAH who decline intravenous therapy will also be considered.

**Table 2 pul212337-tbl-0002:** Summary of eligibility criteria.

**Inclusion criteria:** 1. Able to provide informed consent 2. Age 18–80 years 3. PAH which is idiopathic, heritable, or associated with drugs, toxins, or connective tissue disease 4. Stable PAH therapeutic regime comprising any combination of ERA and PDE5i for at least 1 month before screening (unless unable to tolerate therapy) 5. WHO functional class III 6. Resting mPAP ≥20 mmHg, pulmonary capillary wedge pressure ≤15 mmHg, pulmonary vascular resistance ≥2 Wood Units measured by right heart catheterization at time of diagnosis 7. 6MWT > 50 min at entry 8. eGFR > 30 mL/min/1.73 m² at entry 9. Inadequate treatment response (clinically determined)

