### Statistical analyses

#### Sample size calculation

The sample size was chosen to ensure adequate power to detect differences in the clinical efficacy of the two treatment approaches in population‐level analyses and to have adequate power to evaluate the ability of implantable/remote technology to provide early evaluation of such clinical efficacy. For comparing the clinical efficacy of the two treatment approaches, we have used published RVSV data reporting a minimal clinically important difference of 12 mL and within‐patient standard deviation (SD) of 16.5 mL.^38^ The current study will be powered using a standardized effect (SE) of 12/16.5 = 0.73. Assuming 1:1 randomization of the participants to the two treatment sequences, 40 participants will provide 90% power in the population‐level clinical efficacy analysis for a 5% two‐sided type‐I error rate, with SE of 0.73. This is below the SE previously reported for the pulmonary vascular resistance (PVR; SE = 353.4/219.0 = 1.61),^3^ and the RVEF (SE = 9.12/7.39 = 1.23)^20^ and comparable to that observed for the 6MWT (SE = 36.0/46.7 = 0.77).^6^ Therefore, the study will be well‐powered for population‐level analyses of these additional important outcomes.

The sample size of 40 also provides good power for assessing whether changes in remote physiological measures from baseline to 4 and 8 weeks (mPAP, CO, HR, and heart rhythm) are correlated with changes in clinical measures from baseline to 12 weeks. The sample size of 40 patients provides 90% power, at a two‐sided 5% type‐I error rate, for correlations greater than 0.5, which would represent those of clinical interest.

The study is not powered for formal mediation analysis, so this will be considered exploratory. No formal multiple‐testing correction will be applied.

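### Free improvement: split the period baseline in the primary mixed model, because one slope beside a random participant effect adds avoidable noise to the drug contrast

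*Protocol article*

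**What the plan says.** Under Statistical analysis plan, the primary analysis is a "linear mixed effects model with the dependent variable being the change in RVSV (flow) from baseline to 12 weeks". The article explains there that both time points are those within each treatment period, so each participant can contribute two changes, each with its own baseline. On the covariates it says: "A random effect for each participant will be included together with the within‐treatment period baseline RVSV (flow) measurement, a fixed period effect", together with treatment. The test is a Wald test.

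Under Sample size calculation, the inputs are a "minimal clinically important difference of 12 mL and within‐patient standard deviation (SD) of 16.5 mL". It continues: "The current study will be powered using a standardized effect (SE) of 12/16.5 = 0.73", and concludes that "40 participants will provide 90% power in the population‐level clinical efficacy analysis for a 5% two‐sided type‐I error rate, with SE of 0.73".

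The article does not say whether 16.5 mL is the SD of a single RVSV measurement, of a change, or of a model residual. It gives no between-patient SD and no correlation between baseline and week 12 within a period.

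**The concern.** A change score contains two noisy scans. Covariate adjustment removes the noise of the baseline scan only if the coefficient is the right one for the comparison being made, and in a crossover the drug comparison is made within patients. A high baseline relative to the patient's own level is largely error, and the change should be corrected for it almost fully. A high baseline relative to other patients is largely a real difference in level, and calls for little correction. A random participant effect with a single baseline coefficient lets both sources of information determine one slope. The fitted slope falls between the two, and part of the baseline noise remains in the treatment estimate.

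At stake is the precision of the primary comparison in a trial of 40 patients for which no dropout allowance is stated. The loss comes from the form of the model, not from the data collected.

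**Working it through.** **Inputs from the article:** difference 12 mL, within-patient SD 16.5 mL, N = 40, two-sided 5%, 1:1 to two sequences. **Assumed, because not given:** between-patient SD (s_b) and within-period correlation of baseline and week-12 errors (ρ).

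**1. The stated 90%.** SE = 16.5 × √(2/40) = 3.69 mL; 12/3.69 = 3.25; power = Φ(3.25 − 1.96) = 90.2%. The figure reproduces when each patient supplies one quantity per period with within-patient SD 16.5 mL. That quantity may be a scan or a change; the arithmetic does not distinguish them.

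**2. The two slopes** (change on baseline, 16.5 mL per scan, s_w = 16.5).
- Within patients: ρ − 1, so −1 when ρ = 0.
- Between patients: −(1 − ρ)(s_w²/2)/(s_b² + s_w²/2). With ρ = 0 and s_w²/2 = 136.1, this is −136.1/236.1 = −0.58 at s_b = 10 and −136.1/1361.1 = −0.10 at s_b = 35.

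**3. What a compromise slope costs.** With slope β and k = 1 + β, the within-patient variance left per period is s_w²(1 + k² − 2ρk), and the SE is 3.69 × √(1 + k² − 2ρk). Simulating the model as written (REML, random intercept, Wald z) gave fitted slopes of about −0.76, −0.35 and −0.21 for s_b of 10, 25 and 35 mL at ρ = 0. Putting these in:

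| s_b (mL) | fitted β | 1 + k² | SE (mL) | power by formula | power by simulation |
|---|---|---|---|---|---|
| 10 | −0.76 | 1.058 | 3.79 | 89% | 87–89% |
| 25 | −0.35 | 1.423 | 4.40 | 78% | 78–82% |
| 35 | −0.21 | 1.624 | 4.70 | 72% | 72–75% |

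With the correct within-patient slope, k = 0, the SE returns to 3.69 and power to 90%. Simulation with the participant-mean baseline added gave about 89–92% over the same range of s_b.

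**4. Other readings of the inputs.**
- ρ = 0.3, s_b = 25: fitted β −0.234, k = 0.766, factor 1 + 0.587 − 0.460 = 1.127, SE 3.92, power 87%. Simulated range over s_b: about 83–92%.
- ρ = 0.6, s_b = 25: fitted β −0.132, k = 0.868, factor 1 + 0.753 − 1.042 = 0.712, SE 3.11, power 97%. Simulated range: about 96–98%.
- 16.5 mL as SD of the change, ρ = 0: 16.5/√2 = 11.7 mL per scan. At s_b = 25, fitted β −0.203, k = 0.797, factor 1.635, SE = 11.67 × √1.635 × √(2/40) = 3.34, power 95%. Simulated range: about 92–99%. On this reading an unadjusted change score has SE 3.69 and power 90.2%, the stated figure.

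**5. Bias and validity.** At ρ = 0 the mean treatment estimate under the planned model was 11.9–12.1 mL for a true 12 mL. With s_b = 25 and no true difference, the Wald test rejected in 6.4% of data sets, close to what a z-based Wald test gives at this sample size. These results assume no carry-over into the second baseline.

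**6. Candidate remedies.** Adding the participant-mean baseline matched or beat the planned model, to within simulation error, in all 16 settings compared. Modelling the week-12 value without the period baseline gave about 90% at ρ = 0, but only about 88–93% at ρ = 0.6, where the planned model has 96–98%.

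**The case against.** The strongest reply is that the article never says what 16.5 mL is the SD of. The endpoint is a change within each period. If 16.5 mL is the within-patient SD of that change, the sample size calculation matches the endpoint and the planned model exceeds its stated power. Substantial within-period correlation has the same effect. This stands. A reader might infer from the least favourable case that the primary analysis lacks its stated power; the article does not support that, because the inputs that would decide it are absent. Nor does it support saying that the confidence interval is too narrow: that would need an assumed serial-correlation structure, and nothing in the article points to one.

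A second reply is that Clinical assessments lists MRI only at baseline and Weeks 12 and 27, so there may be no second pre-treatment scan. The baseline would then be constant within a patient and the mechanism could not operate. But the model text defines baseline within each treatment period, and the full visit schedule is in a supplementary table not shown here. The point is taken on the model as stated.

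A third is that the parameterisation of baseline can be left to the analysis plan. It can, but the article already fixes the covariates. It also says that analysis plans are finalised before unblinded data are analysed, so the change may still be open.

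**Conclusion.** The structural point holds: the model as written forces one slope on two relations and loses precision that the same data could supply. The estimate is unbiased, so this is an efficiency matter and a free improvement, not an error that invalidates the analysis.

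The loss matters only on some readings. It reaches about 15 to 18 percentage points (72–75% against 90%) if 16.5 mL is a per-scan SD, within-period errors are uncorrelated and the between-patient SD is as large as 35 mL. It is one to three points at a between-patient SD of 10 mL. With correlation 0.6, or with 16.5 mL as the SD of the change, planned power is above 90% and there is no shortfall against the stated figure. What can be said without assumptions is that the article does not identify the SD, and so does not show that the 90% belongs to the model it specifies.

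**What to change.** Keep change in RVSV (flow) as the outcome and the period baseline as a covariate. Add each participant's mean of the two period baselines as a second covariate, so that the period-baseline coefficient is estimated within patients only. Define the mean for participants with only one period baseline.

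Do not replace the outcome with end-of-period RVSV alone as the preferred remedy: it discards useful baseline information when within-period correlation is high, and it changes the outcome that the article names.

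In the sample size text, state whether 16.5 mL is the within-patient SD of one scan, of a change, or of a residual. Give the assumed between-patient SD and within-period correlation, and restate power for the model to be fitted.

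Cost: one line in the model statement and a short power restatement. No new data are needed, and both changes can be made before unblinded data are analysed.

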## DISCUSSION

Patients with PAH receiving dual combination treatment (PDE5i + ERA) who are stratified as being at intermediate‐low risk^39^ are recommended to intensify therapy via the addition of the IP receptor agonist, selexipag, or to switch from a PDE5i to the sGCS, riociguat.^9^, ^10^, ^29^ There is clinical equipoise between triple therapy with selexipag + PDE5i + ERA and dual therapy with riociguat + ERA. Conducting head‐to‐head clinical trials to compare treatment strategies in patients with PAH is challenging due to the current necessity for repeated, hospital‐based invasive/imaging procedures to evaluate treatment efficacy. Remote hemodynamic and cardiac monitoring may provide a means for early, minimally invasive evaluation of clinical efficacy and early identification of clinical worsening in patients with PAH, which may facilitate study designs evaluating dose–response, time‐to‐effect and head‐to‐head comparison. This study is designed to assess the individualized effect of selexipag and riociguat on RV stroke volume as measured by cardiac MRI, and to determine whether remote monitoring devices can be used to provide an early assessment of the clinical efficacy of drug therapies for PAH. This hybrid drug‐device regulatory‐approved design represents the first evaluation of an sGCS and IP agonist.

This blinded analysis of objective MRI measures provides an efficient, robust, and effective clinical study structure. As the primary endpoint is objective with blinded analysis, patients and clinicians will not be blinded to the sequence of drug allocation and up‐titration.

In this study, data will be relayed daily from regulatory‐approved, minimally invasive monitors to care teams through secure online clinical portals, with the aim of facilitating early, individual‐level, remote evaluation of treatment effects. This study will offer the potential to build on existing evidence showing that remotely monitored parameters may be used at diagnosis to categorize patients with PAH as low, intermediate, or high risk.^24^ In addition to offering the potential for early evaluation of therapies, the use of remotely monitored outcomes may provide a broader picture of the effects of treatment on patients' daily functioning.^25^ Remote patient monitoring may also facilitate more patient‐centric research, and improve study recruitment and retention, which are key issues for research into a rare disease such as PAH.^21^, ^25^ Additionally, patients with PAH are typically prescribed combination therapies, which can make it challenging to power trials to demonstrate the effectiveness of novel therapies.^20^, ^21^

In addition to capturing data on established physiological and biochemical markers of clinical risk, this study will provide valuable insight into patient‐reported quality of life and mental health outcomes, as well as explore side effects experienced during therapeutic up‐titration and withdrawal of therapy.

## ETHICS STATEMENT

IRAS project ID: 325120.

REC reference: 23/NE/0067.

## Data Availability

Data sharing not applicable to this article as no data sets were generated or analyzed as this is a methodological description of a study.
